### Enrollment and assignment

PI or Co-I will obtain the written consent of subjects. The enrollment of subjects who have given their consent and the data of all subjects will be entered into the electronic data capture (EDC) system (Viedoc, PCG Solutions, Uppsala, Sweden). For randomization 1, the subjects will be stratified into two groups (groups A and B as mentioned earlier) according to (1) age (>70 or ≤70 years) and (2) anaerobic threshold (AT) workload (≥30 watts or <30 watts) in the first CPX performed at the time of consent-taking. Randomization 2 will be performed after the intervention period with concurrent cardiac rehabilitation has ended. The stratification factors are (1) the age of the subject (>70 or ≤70 years) and (2) the rate of change in the AT workload in CPX after intervention with concurrent cardiac rehabilitation has ended (≥25% or <25% for group A and ≥15% or <15% for group B).

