### Outcome measures

Primary outcome measure is the rate of change of the AT workload from baseline to post-intervention with concurrent cardiac rehabilitation. Secondary outcome measures include the following: (1) The rate of change from baseline which is performed in the pre-observation period or reference day [Peak VO_2,_ left ventricular EF in the echocardiogram, total points of the Hospital Anxiety and Depression Scale (HADS), muscle strength (grip strength and lower-limb extension power), absolute values of interleukin-6 (IL-6), and tumor necrosis factor (TNF)-α], Time taken for 50% subjects to achieve a 15% improvement in AT workload, which is defined as an event. (2) The rate of change from post-intervention period with cardiac rehabilitation (20 weeks later) to post-single intervention with the BCAA preparation (32 weeks later) [Peak VO_2_, AT workload, total points of HADS, muscle strength (grip strength and lower-limb extension power))], (3) The frequency of serious adverse events (SAEs) throughout the study period.

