### Statistical considerations

The sample size was calculated according to the estimation as follows. We hypothesized that following 6 months of cardiac rehabilitation, there will be an AT workload improvement of 25% (SD: 10%). With the addition of BCAA, we hypothesized that there will be an AT workload improvement of 25% (SD: 10%). Setting the two-sided significance level at5% and power at 90%, the required sample size was 43 cases. Assuming a 5% rate of subjects leaving the study, we chose 48 cases as the target number.

According to the study results, differences (%) in primary outcome between each outcome measurement between A and B groups will be evaluated using the t-test. With respect to differences in outcome measurement (%) in secondary endpoint between groups A and B, the t-test will be used to analyze statistical significance. Similarly, the difference between B-1 and B-2 sub-groups will be analyzed using the t-test. Also,, after confirming the assumption that there are no major differences among the treatment groups (no interaction), the two-way ANOVA will be used to test the treatment effect for addition of a BCAA, and maintenance effect for continuing administration of a BCAA by including group A/B and +1/+2 as factors. A box-plot will be used to visualize primary outcome and secondary outcomes between the 4 groups (A + 1, A + 2, B + 1, B + 2). Finally, defining an AT workload improvement of 15% as an event, a Kaplan–Meier curve will be plotted to compare the curves between groups A and B, and estimate the occurrence of an event rate of 50% of each group.

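### Randomization 2 is stratified by age and AT-workload response, but the week 20–32 tests use neither factor; if these are prognostic, mainly for AT workload, the B-1 versus B-2 t-test is conservative and loses power

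*Protocol article*

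**What the plan says.** All references are to the protocol article.

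- **Enrollment and assignment.** Randomization 2 has two stratification factors. One is age (>70 or ≤70 years). The other is "the rate of change in the AT workload in CPX after intervention with concurrent cardiac rehabilitation has ended", cut at 25% in group A and at 15% in group B.
- **Outcome measures.** The outcomes for the period after rehabilitation are defined as "The rate of change from post-intervention period with cardiac rehabilitation (20 weeks later) to post-single intervention with the BCAA preparation (32 weeks later"), for peak VO2, AT workload, HADS total and muscle strength.
- **Statistical considerations.** For the B subgroups: "Similarly, the difference between B-1 and B-2 sub-groups will be analyzed using the t-test". A two-way ANOVA is to test the effect of adding BCAA and the "maintenance effect for continuing administration of a BCAA by including group A/B and +1/+2 as factors". Neither analysis names age, the response stratum or the week-20 value as a model term.
- **Sample size, same section.** "Setting the two-sided significance level at5% and power at 90%, the required sample size was 43 cases". To allow for a 5% loss, the target was raised to 48. No power is given for any comparison after randomization 2.

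**The concern.** Stratified allocation forces the two arms to be alike on the stratification factors, so the treatment difference varies less from trial to trial than under simple randomization. A t-test that ignores the strata leaves the between-stratum variation in its error term and reports a standard error that is too large for the design. If the factors predict the outcome, the real type I error falls below 5%, confidence intervals are too wide and power is lost.

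For AT workload there is a specific reason to expect some relation. The AT reading at the end of rehabilitation is the end point of the change that defines the stratum and the reference value of the week 20–32 change. A reading that is high by chance raises the first and lowers the second. The A/B term in the ANOVA does not stand in for the stratum, because the response cut lies within each of A and B.

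At stake is the article's named test of BCAA without exercise (B-1 versus B-2) in a small sample, and to a lesser extent the maintenance effect.

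**Working it through.** **The plan's own figure.** The 43 cases belong to the primary A-versus-B test. As printed, both groups improve by 25% (SD 10%), so the difference is 0 and no sample size follows. If 15% is assumed for rehabilitation alone (suggested only by the 15% and 25% cut-points), the total is 2 × 2 × (1.960 + 1.282)² × 10²/10² = 42.03, that is 43. The printed inputs are a separate matter. What counts here is that 43 says nothing about B-1 versus B-2.

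**Inputs**
- Patients: 48/4 = 12 per subgroup, or about 11 after 5% loss. The allocation ratio is not stated; 1:1 is assumed.
- Effect: 1 SD (a 10-point difference with SD 10, on the scale of the primary outcome). Assumption.
- Correlation ρ between the week 20–32 change and the rehabilitation response: not in the documents; 0 to 0.5 is shown.

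**How large ρ could be from the shared reading alone.** Let each change have SD 10 points, each reading carry error e, and true changes be independent. Then ρ = −e²/100, which is −0.25 at e = 5 and −0.49 at e = 7. Each change contains two readings, so error makes up 2e²/100 of its variance: 50% at e = 5 and 98% at e = 7. A size of about 0.5 is therefore the ceiling of this mechanism, not a central value.

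**Power formula, B-1 versus B-2.** Noncentral t, two-sided 5%, 12 per group, residual SD 10√(1−ρ²), 2 degrees of freedom lost when adjusted:
- unadjusted: 64.9%
- adjusted, ρ = 0.25: 67.3%
- adjusted, ρ = 0.5: 76.7%

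With 11 per group, power is 60.7% unadjusted and 72.6% adjusted at ρ = 0.5.

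**Simulation, B-1 versus B-2.** 24 patients, allocation balanced within a median-split response stratum:

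| ρ | Type I error, t-test | Power, t-test | Power, + binary stratum | Power, + continuous response |
|---|---|---|---|---|
| 0 | 4.9% | 65% | 65% | 64% |
| 0.25 | 4.8% | 65% | 67% | 67% |
| 0.5 | 3.3% | 66% | 72% | 76% |

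The adjusted tests stay at about 5% type I error.

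A second simulation used permuted blocks of 2 or 4 within four age-by-response strata. R² is the share of outcome variance explained by response and age together.
- R² = 0: no conservatism; power 65–66% planned, 62–65% adjusted.
- R² = 0.1: type I error 4.0–4.8%; a gain of 2–3 points.
- R² = 0.25: type I error 3.2–3.5%; power 67% planned, 73% with strata, 76–77% with continuous response and age.

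**ANOVA, +1 versus +2 main effect (24 versus 24).** Power at 1 SD is already 92–93% at R² = 0. At R² = 0.25 the type I error is 3.4–3.6%, and power goes from 94% to 96–98% with adjustment. Over the range to R² = 0.5 the loss is about 1–4 points.

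**Effect of the same adjustment on A/B.** Response and week-20 value arise after randomization 1. Suppose A exceeds B by 10 points in rehabilitation and there is no A/B effect in weeks 20–32. The slope on the rehabilitation change is −e²/100, so the adjusted A/B estimate becomes 0 + 10 × e²/100: +2.5 points at e = 5 and +4.9 at e = 7, where the truth is 0. In simulation the shift was of this size, and the +1/+2 estimate stayed unbiased.

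**The case against.** Several points on the other side stand.

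- A reader might infer that the planned tests simply are conservative and lose power. The documents do not support that: they give no correlation, and at zero nothing is lost.
- A reader might also take the whole second aim to rest on about 12 patients per cell. That aim concerns continued administration. B-1 starts BCAA for the first time, and the article assigns the maintenance effect to the ANOVA, which compares about 24 with 24 and loses little.
- The shared-reading argument applies to AT workload only. Peak VO2, HADS and muscle strength share no reading with the stratum, and nothing in the article shows that age is prognostic for them.
- Only part of the gain at ρ = 0.5 (about 7 of 11 points) comes from the stratum itself; the rest comes from using a continuous covariate.
- The week-20 value is not ignored: it is the reference of the change outcome. It is missing only as a covariate.
- The planned tests remain valid in that type I error does not exceed 5%, and these are secondary, exploratory comparisons.

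It could further be said that covariates belong in an analysis plan that is not shown. That does not hold here, because the article itself names the tests and the ANOVA factors.

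**Conclusion.** The mismatch between allocation and analysis is stated in the text, and its direction is confirmed if the factors are prognostic. Its size is conditional. For B-1 versus B-2 at a 1-SD effect it runs from nothing (ρ = 0) through about 1–2 power points (0.25; 2.4 by the formula) to about 7–11 points with a true type I error near 3.3% (0.5, about the most the shared reading alone can produce). For the ANOVA's +1/+2 effect it is about 1–4 points. This rests on 12 per group under 1:1 allocation and a borrowed effect and SD. It is an efficiency weakness in secondary analyses, strongest for AT workload; it does not inflate false positives and does not touch the primary A-versus-B test. It is worth correcting because the covariates are already collected and the change costs little.

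**What to change.** For the week 20–32 outcomes:

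1. **B-1 versus B-2.** Replace the t-test as main analysis with a linear model containing the randomized assignment, the age stratum, the AT response (as stratum or continuous) and the week-20 value of the outcome. For AT workload, use either the response or the week-20 value if degrees of freedom are short. Report the adjusted difference with its 95% confidence interval and keep the t-test as a sensitivity analysis.
2. **Four-group model.** Use this adjustment only for the +1/+2 effect, with the response stratum coded within A and B because the cuts differ.
3. **A/B effect.** Take it from a model without the week-20 value, rehabilitation change or response stratum.

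The cost is wording plus a few residual degrees of freedom: 22 for the t-test, against 20 with age and response and 19 with the week-20 value as well. If the factors are not prognostic, that costs about 1–3 power points.

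### The two-way ANOVA depends on confirming no interaction, which 11–12 patients per cell cannot do, and its pooled +1/+2 term is not the effect of continuing BCAA

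*Protocol article*

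**What the plan says.** All references are to the protocol article.

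- **Design (Study methods).** Patients are randomized to A (rehabilitation plus BCAA) or B (rehabilitation alone). They are then re-randomized: A-1 continues BCAA, A-2 stops it, B-1 starts it and B-2 never receives it.
- **Timing (Enrollment and assignment).** "Randomization 2 will be performed after the intervention period with concurrent cardiac rehabilitation has ended". It is stratified by age and by the change in AT workload over rehabilitation, cut at "≥25% or <25% for group A and ≥15% or <15% for group B".
- **Aims (Aim).** The second aim is to explore whether BCAA continued after rehabilitation preserves cardiopulmonary and skeletal muscle function.
- **Outcomes (Outcome measures).** The primary outcome is the change in AT workload from baseline to the end of rehabilitation. A separate set of secondary outcomes, including AT workload, runs from week 20 to week 32.
- **Analysis (Statistical considerations).** A versus B and B-1 versus B-2 are compared by t-test. Then, "after confirming the assumption that there are no major differences among the treatment groups (no interaction), the two-way ANOVA will be used", with A/B and +1/+2 as factors, to test the effect of adding BCAA and the maintenance effect of continuing it. The sentence names no outcome. Also, "A box-plot will be used to visualize primary outcome and secondary outcomes between the 4 groups".

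**The concern.** There are three linked difficulties.

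1. The model is allowed only once no interaction has been confirmed. At this sample size a check that finds nothing says little, yet it would license a single pooled +1/+2 effect for both arms.
2. The pooled +1/+2 term is labelled as maintenance through continued BCAA. Continuation happens only in group A; in group B the same factor level means first exposure.
3. Because the outcome is not named, the two labels cannot both be matched to either AT-workload change that the protocol lists.

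At stake is the second aim. Group B has its own stated t-test. For continuation in group A, this conditional ANOVA is the only test the article states, so a pooled result could be reported as a maintenance effect when it is partly, or even wholly, an effect of starting BCAA.

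**Working it through.** **Inputs**

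- Target size: "Assuming a 5% rate of subjects leaving the study, we chose 48 cases as the target number". Completers: 48 × 0.95 = 45.6.
- Four cells. Equal allocation is an assumption, since no ratio is stated. 48/4 = 12 enrolled and 45.6/4 = 11.4 completing per cell, so n = 11 and n = 12 are used.
- SD 10 points, from the sample-size paragraph. It refers to AT change over rehabilitation; applying it to the second period is an assumption.
- A 10-point effect as yardstick. It is inferred, not printed: the sample-size paragraph gives 25% for both groups, and the 25% and 15% cut-offs at randomization 2 suggest the intended means.

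**Step 1: the plan's own figure.** "Setting the two-sided significance level at5% and power at 90%, the required sample size was 43 cases". With the printed means the difference is 0 and no sample size exists. With 25% versus 15% and SD 10, the total is 4 × (1.960 + 1.2816)² = 42.03, or 43 rounded up. So 43 fits a 10-point difference. The identical printed means are a separate matter, and this point does not depend on them.

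**Step 2: precision of the interaction.** The contrast is (A-1 − A-2) − (B-1 − B-2), with SE = SD × √(4/n) and df = 4n − 4.

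- n = 11: SE = 10 × √(4/11) = 6.03; 95% half-width = 2.021 × 6.03 = 12.2 points.
- n = 12: SE = 10 × √(4/12) = 5.77; 95% half-width = 2.015 × 5.77 = 11.6 points.

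Even an observed interaction of exactly zero leaves ±10 points inside the 95% CI.

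**Step 3: power of an interaction test** (noncentral t, noncentrality = interaction/SE, two-sided 5%, SD 10).

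| True interaction | n = 11 | n = 12 |
|---|---|---|
| 5 points | 13% | 14% |
| 10 points | 37% | 40% |
| 15 points | 68% | 72% |
| 20 points | 90% | 92% |

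At a 10% level, power for 10 points is 49.5% and 52.5%. If the SD were 15 to 20 points (assumed range), power for 10 points at the 5% level would be about 13% to 20%. At SD 10, 80% power for 10 points needs 32 per cell (128 in total), and 90% needs 43 per cell (172).

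**Step 4: what the pooled term estimates.** Let c be the effect of continuing (A-1 − A-2) and s the effect of starting (B-1 − B-2). In a balanced layout the pooled term is (c + s)/2 and the interaction is c − s. The pooled term therefore misses c by (c − s)/2, half the interaction. With a zero observed interaction, the 95% CI still allows a gap of 12.2/2 = 6.1 or 11.6/2 = 5.8 points between the pooled term and the continuation effect.

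**Step 5: labels against possible outcomes.**

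| AT-workload outcome | A/B term | +1/+2 term |
|---|---|---|
| Baseline to end of rehabilitation (listed, primary) | Effect of adding BCAA | Assigned afterwards; can have no effect |
| Week 20 to 32 (listed) | Carry-over of first-period BCAA | Correctly timed, but mixes continuing and starting |
| Baseline to week 32 (not listed for AT) | Estimable | Estimable, same mixture |

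On the primary outcome the +1/+2 test would also be off its level, because randomization 2 is stratified on that outcome. In 8,000 simulated trials (48 patients, assignment balanced within the AT-change strata, age ignored) it was significant in 0.1% of runs, against 4.8% with unstratified assignment.

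**The case against.** Several stronger readings are tempting, and the other side is right to resist them.

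- **That the plan tests +1/+2 on an outcome measured before it is assigned.** The ANOVA sentence names no outcome, and the primary outcome has its own A versus B t-test. The only pointer is the four-group box-plot of the primary outcome, which is descriptive and can serve as a balance check at randomization 2. The timing objection holds only if the primary outcome is the ANOVA outcome.
- **That one ANOVA can never test both effects.** Two successive randomizations form a 2×2 layout, and a baseline-to-week-32 change could carry both factors. What stands is that no such AT outcome is listed and that neither listed AT change fits both labels.
- **That only pooled results will be reported.** An unconditional B-1 versus B-2 t-test is already planned. A-1 versus A-2 is what is absent.
- **That a stated share of trials would wrongly pass the check.** Such a figure needs a pass rule, and the article gives no test, level or margin. If the rule were p ≥ 0.05 and the true interaction 10 points, about 60–63% of trials would pass; both conditions are assumptions. An article may leave the criterion to the analysis plan, so its absence is not the point.
- **That passing the check biases the pooled estimate.** In a balanced 2×2 layout the pooled estimate is orthogonal to the interaction and remains a correct average. The fault is in reading that average as the continuation effect.

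The post-rehabilitation aim is also worded as exploratory, which limits the consequence.

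**Conclusion.** The point holds for the second-period analysis. With 11–12 per cell the interaction is known only to about ±12 points. A check at that size is reliable only for interactions near 20 points (90–92% power), twice the inferred treatment effect. Because the second factor means different things in A and B, interaction is plausible from the design alone, and the pooled +1/+2 term should not carry the maintenance label. The direct test of continuation, A-1 versus A-2, should be stated. On the week 20–32 change, A/B should not be called the effect of adding BCAA to rehabilitation.

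The figures rest on equal allocation, on the SD of 10 points carrying over to the second period, and on a 10-point yardstick inferred from the randomization 2 cut-offs. A larger SD would make the check weaker still. The label problem depends on none of these figures. A reader might infer that the primary comparison is compromised; the documents do not support that, since it is a separate t-test on an outcome fixed before randomization 2.

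**What to change.** - Drop the condition that no interaction be confirmed.
- Assess adding BCAA by A versus B on end-of-rehabilitation outcomes only.
- For week 20–32 outcomes, fit one model with the week-20 value, the randomization 2 stratification factors (age, and AT-change stratum coded with each arm's own cut-off), first-period arm, second-period assignment and their interaction.
- Report A-1 minus A-2 (continuing), B-1 minus B-2 (starting) and the interaction, each with a 95% CI, whatever the interaction p-value.
- Do not label the A/B term in that model as the effect of adding BCAA.
- Keep four-group box-plots of the primary outcome only as a balance check at randomization 2.

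This changes wording only and needs no further patients or visits. The cost is precision. Before covariate adjustment, at SD 10 and n = 11, an arm-specific half-width is 2.021 × 10 × √(2/11) = 8.6 points, against 2.021 × 10 × √(1/11) = 6.1 for the pooled term. At n = 12 the figures are 2.015 × 10 × √(2/12) = 8.2 and 2.015 × 10 × √(1/12) = 5.8. A two-sample t-test of a 10-point difference within one arm has 61% power (11 per cell) or 65% (12 per cell). The wider intervals show what the trial can support on continuation.

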### Study methods

This is a randomized, active-controlled, parallel-group comparative study. Study outline is presented in Fig. 1. The study consists of three periods—pre-observation, intervention with concurrent cardiac rehabilitation, and BCAA single intervention. In pre-observation period (Day 1 to Week 4), the consent of patients undergoing cardiac rehabilitation at the hospital for CHF will be obtained, and their eligibility will be determined by blood tests and imaging tests (echocardiogram). In the period of intervention with concurrent cardiac rehabilitation (for 18–22 weeks), patients who are confirmed eligible for study enrollment will be randomized into either group A (CR + BCAA) or group B (CR). BCAA is orally supplemented with one pack of BCAAs granules (Aminovact Combination Granules ®, Nichi-Iko Pharmaceutical Co, Toyama, Japan) which includes 1144 mg of L-valine, 1904 mg of L-leucine and 952 mg of L-isoleucine, two times a day. Cardiopulmonary exercise test (CPX) will be performed on each subject in both groups before intervention with the BCAA preparation as well as at Week 14 and Week 20 of the intervention with cardiac rehabilitation. In the BCAA preparation single intervention period (20–24 weeks), re-randomization, i.e., randomization 2, will be performed after the cardiac rehabilitation program has ended. Subjects in group A will be assigned to Group A-1 or A-2, whereas those in Group B will be assigned to Group B-1 or B-2. As described in Fig. 1, subjects assigned to Group A-1 will continue the BCAA preparation. Similarly, subjects in Group B-1 will start taking the BCAA preparation. The BCAA preparation will be discontinued for subjects assigned to Group A-2, and subjects in Group B-2 will not undergo intervention with the BCAA preparation throughout the study period.

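### In the rehabilitation period AT workload is tested after baseline only at Weeks 14 and 20, so the Kaplan–Meier time for 50% of patients to improve by 15% is essentially a visit date, and no horizon is stated

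*Protocol article*

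**What the plan says.** All of this is in the protocol article.

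- **Outcome measures** lists as a secondary outcome: "Time taken for 50% subjects to achieve a 15% improvement in AT workload, which is defined as an event".
- **Statistical considerations** fixes the method: "defining an AT workload improvement of 15% as an event, a Kaplan–Meier curve will be plotted". Its purpose is to "compare the curves between groups A and B, and estimate the occurrence of an event rate of 50% of each group".
- **Study methods** gives the timing of the cardiopulmonary exercise test (CPX), which yields AT workload: "before intervention with the BCAA preparation as well as at Week 14 and Week 20 of the intervention with cardiac rehabilitation". The length of that period varies: "In the period of intervention with concurrent cardiac rehabilitation (for 18–22 weeks".
- **Outcome measures**, item (2), also needs AT workload at a later point: "post-single intervention with the BCAA preparation (32 weeks later". By then the second randomisation has taken place: "Subjects in group A will be assigned to Group A-1 or A-2, whereas those in Group B will be assigned to Group B-1 or B-2".

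The article gives no horizon for the time-to-event outcome, does not mention interval censoring, and does not say whether nominal weeks or actual test dates are the time scale.

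**The concern.** Kaplan–Meier takes each event time as known exactly, apart from right censoring. Here improvement happens at an unseen moment and is detected at the next scheduled test. If the detection date is entered as the event date, the curve steps at the visits and its 50% point describes the appointment calendar.

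The stake is how a named secondary outcome will be read. A median in weeks looks like a statement about how fast patients improve, and a difference in medians looks like faster benefit from BCAA. The planned tests cannot support that reading. A large true difference inside the first 14 weeks would be invisible, and a trivial one that straddles Week 14 would look like six weeks.

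The missing horizon adds a second problem. If follow-up for this outcome runs on to 32 weeks, late events in A and B arise among patients re-randomised to BCAA or no BCAA, and the curve no longer compares the first-period treatments alone.

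**Working it through.** The article gives no numerical figure for this outcome, so there is none to reproduce. The sample-size figure in the same section is not an input here.

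**1. What is observed.** AT test times in the rehabilitation period are 0, 14 and 20 weeks (Study methods). The time T of first reaching 15% is known only as T in (0,14], T in (14,20], or T > 20.

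**2. What the 50% time becomes.** Let F(t) be the true proportion who have reached the event by week t. Recorded at the visits, and ignoring dropout, the median is
- 14 if F(14) ≥ 0.5,
- 20 if F(14) < 0.5 ≤ F(20),
- not reached if F(20) < 0.5.

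**3. Loss of information.** Assume, for illustration only, exponential event times with true median m that are never lost once reached. Then F(t) = 1 − 2^(−t/m).

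| True median m (weeks) | F(14) | F(20) | Recorded median |
|---|---|---|---|
| 3 | 0.961 | 0.990 | 14 |
| 7 | 0.750 | 0.862 | 14 |
| 10 | 0.621 | 0.750 | 14 |
| 13.9 | 0.502 | 0.631 | 14 |
| 14.1 | 0.498 | 0.626 | 20 |
| 17 | 0.435 | 0.558 | 20 |
| 19.9 | 0.386 | 0.502 | 20 |

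Medians of 3 and 13.9 weeks, a difference of 10.9 weeks, give a recorded difference of 0. Medians of 13.9 and 14.1 weeks, a difference of 0.2, give a recorded difference of 20 − 14 = 6. The exponential shape fixes the F values. The mapping of medians to visits follows from step 2 for any distribution.

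**4. Actual dates.** If test dates replace nominal weeks, the values spread around the visits. Assuming the second test moves with the end of an 18–22 week period, its date can range over 22 − 18 = 4 weeks without any difference in when patients improved.

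**5. Under the printed planning figures.** Statistical considerations prints a mean AT gain of 25% with SD 10% for both groups. Assuming normality, P(gain ≥ 15%) at the end of rehabilitation = Φ((25 − 15)/10) = Φ(1) = 0.84. A simulation with 24 per group assumed a within-patient correlation of 0.7 and a Week 14 mean of 70% to 100% of the Week 20 mean. The recorded median was 14 in about 89% to 100% of trials. Both groups would then usually show 14 weeks.

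**6. Horizon.** With follow-up cut at the end of rehabilitation, the nominal values are 14, 20 or not reached. If the later test counts, 32 is added. Patients in A and B who first reach 15% at 32 weeks do so after assignment to A-1, A-2, B-1 or B-2, so that test adds events but no clean A versus B information.

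**The case against.** The strongest reply is that both groups share one visit schedule, so coarse timing alone does not bias A against B. The plan also compares curves, not only medians. A curve read at Weeks 14 and 20 estimates cumulative attainment and handles dropout, which is close to what is proposed below. The outcome is secondary, in a trial whose stated aim is to explore. All of that stands. It limits the importance of the point, but it does not give meaning to a 50% time in weeks, which both sections name explicitly.

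Two stronger readings are tempting, and the article does not support them.

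- **That the median can only be 14, 20 or not reached.** This overlooks the AT test at 32 weeks and the absent horizon, and it holds only on a nominal time scale. The restriction applies to the rehabilitation period, and even there in essence only.
- **That about half of group B will never have an event by Week 20, so that its median is reached in only 50–58% of trials.** This needs a control mean of 15%, which the article never states. It can only be inferred from the cut-offs for the second randomisation, while the printed figure is 25% for both groups. It also counts Week 20 status alone, whereas the planned event is first attainment. Even with an assumed mean of 15%, SD 10% and correlation 0.7, P(event by Week 20) = 1 − P(below 15% at both visits) = 0.56 to 0.63 as the Week 14 mean runs from 70% to 100% of the Week 20 mean. The median is then reached in about 70% to 93% of trials with 22 to 24 patients. Neither figure should be used.

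The schedule table is not shown in this copy, but the text of Study methods states the CPX times plainly.

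**Conclusion.** The point holds for the rehabilitation period. The stated tests cannot deliver the stated summary: the 50% time will be a visit date or not reached, with any scatter due to scheduling. This is a fault in an analysis the article spells out, not a detail left to a fuller document. In size, all true medians up to 14 weeks are indistinguishable, as are all those above 14 and up to 20. That conclusion rests only on the visit schedule and on events being recorded at the test. The 89% to 100% figure rests in addition on the printed 25% (SD 10%) and the assumed normality, correlation and Week 14 mean.

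The missing horizon is part of the same point, because the only later AT test the article names falls after re-randomisation. A reader should not infer that the A versus B comparison is biased by the coarse timing, or that the primary outcome is touched. The change is worth making before analysis, but it concerns one secondary outcome.

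**What to change.** Amend Outcome measures and Statistical considerations together:

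1. State that this outcome ends at the Week 20 CPX and that the 32-week test does not count towards it.
2. Replace the time for 50% by the proportion with at least 15% AT improvement at Week 14 and at Week 20, with the A minus B risk difference and 95% CI at each visit. Cumulative first attainment by each visit is an acceptable alternative. It is a different quantity, since a patient may reach 15% at Week 14 and fall below it by Week 20, so the text should name which is meant.
3. If a curve is wanted, use an interval-censored (Turnbull) estimate with intervals (0,14], (14,20] and beyond 20 weeks, and report no median in weeks.

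The data are the same and no extra tests are needed. The cost is an amendment to a secondary outcome in an approved protocol and the loss of a single time summary.
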